13. ANNEXES……………………………………………………………………………………31

**SUMMARY**

**Rationale:** Birt-Hogg-Dubé syndrome (BHD) is a rare autosomal dominant disorder characterized by the occurrence of benign, mostly facial, hair follicle tumours called fibrofolliculoma, multiple lung cysts and (probably as a result) spontaneous pneumothorax and kidney cancer. The fibrofolliculomas can be quite disfiguring and are usually the reason that patients come to medical attention**.**

A topical treatment for chronic use that reduces the number of tumours and/or prevents the growth of new ones would be preferable but is not yet available.

Research on mouse models and our own human data suggest that in BHD syndrome there is deregulation of mTOR signalling. mTOR, mammalian target of rapamycin, is a multiprotein-complex that is a central player in cellular growth regulation and energy sensing. We think that in BHD the mTOR protein is upregulated or overactivated which causes tumour growth, including fibrofolliculomas. This would mean that mTOR inactivation could prevent growth of fibrofolliculomas. New insights from genetic and cell biological studies now suggest a potential therapy; the mTOR inhibitor rapamycin. Rapamycin oral solution has been used topically in previous studies and was both safe and effective. Thus, we have theorized that rapamycin oral solution might be used safely topically for the treatment of BHD-associated fibrofolliculomas.

**Objectives**: Primary objective: To determine whether topical application of rapamycin can lead to reduction in size and/or number of fibrofolliculomas in BHD patients and may prevent the growth of new ones. Secondary Objectives: Safety, formula acceptance and patient satisfaction.

**Study design:**Double-blind placebo-controlled randomized intervention study.

**Study population:** Otherwise healthy patients ≥ 18 years of age with genetically proven Birt-Hogg-Dubé syndrome and facial fibrofolliculomas.

**Intervention**: Application of rapamycin 1 mg/ml oral solution to one predefined skin area on one facial half, twice daily. The other facial half will be similarly treated with a placebo.

**Main study endpoints:** The main study parameter is significant regression (reduction in facial fibrofolliculoma size and count) in the treated area due to topical rapamycin. Secondary endpoints are the absence of any effect, tolerability, adverse events, formula acceptance and patient satisfaction.

**Nature and extent of the burden and risks associated with participation, benefit and group relatedness:** Participation requires patients to apply rapamycin liquid and placebo liquid twice daily. Participation in the study will take the patient 5 minutes a day, plus the 4 control visits that will take approximately 30 minutes. A potential risk when participating in this study is an allergy for one of the components of rapamune oral solution. Furthermore, local irritation due to the excipient, which contains alcohol, is possible but this can be easily controlled with emollients. There will be one biopsy for patients who have not yet undergone one. A skin biopsy is taken by means of a 3 mm punch after injection of local anaesthetic which is briefly painful. A properly taken biopsy will leave no or minimal scarring. Previous studies have shown that topical application of rapamycin is safe and does not lead to therapeutic plasma levels. The benefit for the patients is in the potential reduction in facial tumour size and number. For BHD patients in general the benefit will be an easily used topical treatment with which fibrofolliculomas may be treated or prevented.

# 1. INTRODUCTION AND RATIONALE

Birt-Hogg-Dubé syndrome (BHD) is a rare autosomal dominant disorder characterized by the occurrence of benign, mostly facial, hair follicle tumours called fibrofolliculoma [1], multiple lung cysts and (probably as a result) spontaneous pneumothorax [2] and an increased renal cancer risk [3-5]. The fibrofolliculomas (FF) can be quite disfiguring and are usually the reason that patients come to medical attention. FF usually appear after the age of 25 years and are progressive. Typically presenting around the nose, they can spread onto the ears, neck and trunk. [1] Although they do not grow beyond 3-4 mm in size, their numbers increase with age so that patients can eventually have hundreds of tumours. Presently, ablative laser is the preferred treatment. In addition, surgical interventions, like excision and shaving, and elektrocoagulation are performed. Disadvantages of these treatments are the risk of complications (scarring, inflammation, hypo-and hyperpigmentation) and recurrence (for laser therapy it is known that FF recur after 2-3 years or even after months [6].) Moreover, these treatments do not prevent the growth of new FF. A topical treatment that is suitable for chronic use and reduces the number of tumours and/or prevents the growth of new ones would be preferable but is not yet available. New insights from genetic and cell biological studies now suggest a potential topical therapy. BHD syndrome is caused by germline mutations in the BHD gene coding for the protein folliculin [7]. Strongly conserved in evolution, folliculin’s function is mostly unknown. We now know, from research on mouse models and our own human data, that in BHD syndrome there likely is deregulation of mTOR signalling [8]. mTOR, mammalian target of rapamycin, is a multiprotein-complex that is a central player in cellular growth regulation and energy sensing [9]. The mTOR pathway consists of two major branches, each mediated by a specific mTOR complex (mTORC). The first complex, mTORC1, controls several pathways that collectively determine the mass (size) of the cell. The second complex, mTORC2 controls the actin cytoskeleton and thereby determines the shape of the cell [10]. mTORC1 and possibly mTORC2 respond to growth factors (insulin/IGF), energy status of the cell, nutrients (amino acids), and stress [10], as seen in the figure below. Thus, BHD syndrome belongs in a larger family of disorders characterized by mTOR deregulation, such as tuberous sclerosis complex (TSC) [9, 11]. In TSC, as in BHD, patients develop facial hair follicle tumours called angiofibroma. These tumours strongly resemble fibrofolliculoma and are increasingly seen as a variant of the latter. Very recent findings indicate that angiofibromas of TSC respond favourably to the mTOR inhibitor rapamycin – they disappear after only a few months of oral rapamycin [12]. The action of rapamycin is as follows.Studies in rapamycin activity have shown that it requires an intracellular co-factor, FKBP12 (FK506-binding protein 12). Rapamycin and FKBP12 together form a complex, FKBP12-rapamycin. It has been demonstrated that this complex binds to and inhibits mTORC1 [13](see figure 1). The exact way in which this happens is not yet clear. However, there is a hypothesis that FKBP12-Rapamycine changes the conformation of the raptor-mTOR complex and thereby strongly destabilizes it [10, 14].

# Oral administration has potential side effects that are not acceptable in the context of BHD syndrome. However, there are several studies showing that topical application is safe and may be a feasible strategy. Rapamycin oral solution 1 mg/ml has already been used off-label for non-related mucosal and skin disorders and was both safe and effective, with no significant systemic resorption, when applied topically [15, 16]. Thus, we have theorized that rapamycin oral solution might be used for the treatment of BHD-associated fibrofolliculomas.

#
[figure not shown]

# Figure 1. mTOR pathway

# 2. OBJECTIVES

Primary Objective:

To determine whether topical application of rapamycin 0.1% solution can lead to reduction in size and/or number of fibrofolliculomas in BHD patients and may prevent the growth of new ones.

Secondary Objectives:

To assess safety, formula acceptance and patient satisfaction.

# 3. STUDY DESIGN

The study is double-blind placebo-controlled randomized with the patient him/herself as an internal control. To get enough power we aim to include 20 (see power analysis) adults ≥18 years with Birt-Hogg-Dubé syndrome. Inclusion will take place in two hospitals in the Netherlands; Maastricht University Medical Centre and VU Medical Centre Amsterdam. After inclusion patients are treated with rapamycin in one facial half and a placebo in the other. Patient and physician are blinded until the end of the study. The solution (placebo and verum) is applied according to standardized instructions. The study will proceed according to standardized trial monitor forms (Annex F4). These forms describe how the patient is to be examined at each visit. The skin will be evaluated by 3 observers; the investigator and two dermatologists. They will assess a difference in fibrofolliculoma status on a 7-point rating scale ranging from -3 (strong worsening) to +3 (strong improvement). Although patients evaluate their skin on this scale too, we will not include their measurements in the analysis because of bias. For further explanation see chapter 7.

Patients will be followed-up at 3 months and at 6 months.

It is likely that, during the study, one facial half will improve because of treatment with rapamycin. However, we do not think it is ethical to ask our patients to deal with one improved facial half and one unimproved facial half. Moreover, when patients see a difference between facial sides, they might apply the solution, that they think is the effective one, on both facial sides. To prevent this situation we developed the following study design:

When a clear difference arises between facial sides, blinding will be broken and we will proceed with an open-label study. There are a few conditions to break the blinding, pointed out below.

- Two of three observers have to see a significant difference. This means that there must be an improvement (or worsening, which we don’t expect) of at least 2 points on the 7 point rating scale.
- When there is a significant difference, the blinding will be broken. Then it will also become clear whether the improved side is the rapamycin-treated side. In this case patients are allowed to use rapamycin on the entire face.
- When patients see a difference between the left and right facial side themselves, they can make an earlier appointment.
- To prevent a large proportion of patients form dropping out at an early stage of the study, we aim to continue treatment for at least 3 months. When patients contact us before the end of this period, we will try to motivate them to continue treatment.
- It is also possible that patients see a moderate or strong improvement, while the observers just see a minimal one. Also in this case we will try to motivate patients to proceed with the study for one more month.

In the last two situations described above it will be difficult to convince patients to continue treatment before blinding is to be broken. We think that a good explanation of the importance of the trial and the benefits for the patient, will help to retain patient adherence. Of course we prefer to continue the study as long as possible. However, when a patient really wants to stop treatment due to a clear difference between facial halves, we will break the blinding.

Although we don’t expect it, rapamycin might worsen skin lesions in individual patients. In this situation, the trial will end, just for this specific patient. Another condition to terminate the study prematurely for a specific patient is when it turns out that rapamycin has no effect at all. In our opinion, rapamycin has no effect when no improvement has occurred after 3 months. We base this 3 month period on several clinical studies in which rapamycin was used for treatment of dermatological diseases. In these studies, the effect of rapamycin was visible within 3 months [12, 15-17].

See Annex F4 for a flow chart that gives an overview of the procedures that subjects undergo and a flow chart for patients. Procedures are also described in chapter 7.

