## 4.4 Sample size calculation

Sample size is calculated to detect a difference of 35% in response as measured with a 7-point scale with a power of 90% and a type 1 error, 2 sided, of 0.05. Using McNemar’s chi-square test for matched pairs (each patient serves as his/her own control) we would need 17 patients. Taking into account 15% drop-outs we need to include 20 patients.

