# *7.* METHODS

## 7.1 Study parameters/endpoints

### 7.1.1 Main study parameter/endpoint

The main study parameter is the change in lesion size and count (severity) as measured by the investigator, the patient and two independent dermatologists. For lesion size we use the average size of fibrofolliculomas in millimetres.

Severity is indicated on a 7-point scale:

-3= strong worsening

-2= moderate worsening

-1= minimal worsening

0= no improvement

1= minimal improvement

2= moderate improvement

3= strong improvement

Significant regression is defined as a difference in assessment by at least 2 of 3 observers, with at least +2 points. The observers are the investigator and two independent physicians. Assessment of size and count is made on the basis of medical photos of the face. These photos will be standardized; same distance, background, colour and light profile etc.

Confirmation by visual examination.

Professor [name], professor in clinical epidemiology of Maastricht UMC has advised us to use this 7-point scale. Given the fact that there are no previous randomized controlled trials in the BHD syndrome, there is no previously validated scale that we can use for this disease. That is why we have chosen for a 7-point Likert scale. It is known that the Likert scale has good measurement properties and it is used often in trials in which skin changes have to be assessed [19, 20].

During the study we will determine the intra- and inter-observer variability by means of a weighted kappa test. Per patient 2 photographs will be assessed with the 7-point scale; at 3 months and at 6 months. These photographs will be compared with a baseline photo. To measure the inter- and intra observer variability we need at least 3 observers. These observers will be the researcher and two independent physicians. They will assess every photo twice. To prevent bias, the assessments must be at least 2 months apart. Besides evaluation based on photographs, the researcher as well as the patient can assess facial progress during the appointments. These assessments are not included in the analysis, only the results based on the photographs provided by the researcher, physician 1 and physician 2 will be used. This means there will be 6 scores for every patient per follow-up visit. Of these results, the most frequently given score will be used for the analysis.

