## 7.5 Replacement of individual subjects after withdrawal

To have enough power we need at least 17 patients. When the number of patients drops below 17, we will replace them by new subjects.

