## 9.2 Primary analysis

During the trial patients apply rapamycin solution in one facial half and placebo solution in the other facial half. This means that the patient is his/her own control.

Primary output measure is change in facial fibrofolliculoma size and count (severity) as measured by the investigator, two independent physicians and the patient. The response to treatment will be assessed with a 7-point rating scale, ranging from -3 (strong worsening) to +3 (strong improvement). This scale is described in chapter 7. Significant regression is defined as assessment by at least 2 of 3 observers with at least +2 points. Rapamycin will be compared with placebo using a McNemar ‘s chi square test for paired samples. Both an intention to treat and a per protocol analysis will be performed.

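### No primary visit is named for the McNemar comparison, although responders may treat the control half from about month 3, so a 6-month analysis would be diluted in the pairs that carry the information

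*Protocol*

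**What the plan says.** **Switching.** Under Section 3 the blind is broken when two of three observers see a change of at least 2 points on the 7-point scale. If the better side is the rapamycin side, "In this case patients are allowed to use rapamycin on the entire face"; Section 7.2 adds that the study then continues open label. Section 7.3 places the check at the 3-month visit, and Section 3 lets patients come earlier.

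**Stopping.** Section 3 also provides: "Another condition to terminate the study prematurely for a specific patient is when it turns out that rapamycin has no effect at all". It takes no improvement after 3 months as the criterion. Section 7.5 adds: "When the number of patients drops below 17, we will replace them by new subjects".

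**Measurement and analysis.** Section 7.1.1 states: "Per patient 2 photographs will be assessed with the 7-point scale; at 3 months and at 6 months". Each photograph is compared with baseline, and the modal score per follow-up visit goes into the analysis. Response means at least +2 points from at least 2 of 3 observers. Section 9.2 describes one McNemar comparison and says: "Both an intention to treat and a per protocol analysis will be performed". Sections 4.4, 7.1.1, 9.1 and 9.2 name no primary visit, and none says how a half that has switched to open-label rapamycin is to be handled.

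**The concern.** McNemar's test uses only discordant pairs, here patients in whom one half responds and the other does not. The unblinding threshold is in effect the response threshold. The patients who form rapamycin-favouring pairs at month 3 are therefore the ones who may put rapamycin on the control half.

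If month 6 is the visit analysed, an intention-to-treat comparison may set rapamycin against rapamycin in these patients. A per-protocol set that excluded both switched and stopped patients would keep mainly those with an intermediate result. A drug that works quickly could then weaken its own 6-month contrast.

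With two scored visits and no choice between them, the visit can also be chosen after the results are known. The investigator is one of the three photograph raters and would probably know the allocation of unblinded patients when scoring their 6-month photographs.

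**Working it through.** **Inputs from the protocol (Section 4.4).** "Sample size is calculated to detect a difference of 35% in response as measured with a 7-point scale with a power of 90" per cent; "a type 1 error, 2 sided, of 0.05"; "we would need 17 patients"; 15% drop-out, giving 20 enrolled. No placebo response rate or discordant proportion is given.

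**Step 1: reproduce the planned figure.** Suppose no placebo half responds. Every discordant pair then favours rapamycin, and their number X is binomial with n = 17 and p = 0.35. The uncorrected statistic is (b − c)²/(b + c). With c = 0 it equals b, so rejection needs b > 3.84, that is at least 4 pairs.

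- Power = P(X ≥ 4) = 0.897, which matches the stated 90%.
- Expected discordant pairs: 17 × 0.35 = 5.95.
- Enrolment: 17 / 0.85 = 20, as stated.

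This is the most favourable reading. An exact or continuity-corrected test needs 6 pairs, and its power at n = 17 is 0.58. That is a separate matter; the uncorrected test is used below so that the comparison starts from the protocol's own 90%.

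**Step 2: use the 6-month photographs after the switch.** Let q be the share of switched patients whose former control half also reaches +2 by month 6. The protocol gives no value, so q is assumed over its whole range. All month-3 responders are taken to switch, and no one is taken to respond later. A patient who catches up becomes a concordant pair, so p = 0.35 × (1 − q) and power = P(Bin(n, p) ≥ 4).

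| q (assumed) | Remaining difference | Expected discordant pairs, n = 17 | Power, n = 17 | Power, n = 20 |
|---|---|---|---|---|
| 0 | 35 points | 5.95 | 0.90 | 0.96 |
| 0.25 | 26 points | 4.46 | 0.69 | 0.81 |
| 0.50 | 17.5 points | 2.97 | 0.35 | 0.47 |
| 0.75 | 9 points | 1.49 | 0.06 | 0.09 |
| 1 | 0 | 0 | 0 | 0 |

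**Step 3: allow placebo responders and late response.** Assume 40% rapamycin-only and 5% placebo-only responders at month 3 and n = 20. Assume also that half of the remaining 55% continue blinded and 15% of those respond later on the rapamycin half. Late response adds 0.55 × 0.5 × 0.15 = 0.041 to the rapamycin-only share. The month-6 difference is 0.40 × (1 − q) + 0.041 − 0.05, that is 39, 29, 19, 9 and −1 points for q = 0, 0.25, 0.50, 0.75 and 1. Simulated power of the uncorrected test is about 0.70 at month 3. At month 6 it is about 0.77, 0.59, 0.36, 0.13 and below 0.01. Month 6 is the better visit only if there is little catch-up.

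**Step 4: the comparison proposed under the fix.** On the last blinded photograph the switch cannot dilute the contrast. Under the Step 1 assumptions power stays at 0.897 for n = 17 and 0.956 for n = 20.

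**The case against.** Much can be said for the plan. It does not state outright that post-switch 6-month scores enter the McNemar test: Section 7.1.1 introduces the two photographs alongside observer variability, and Section 9.2 is silent on the visit. Whole-face use is allowed, not required. The month-3 contrast survives wherever no earlier unblinding took place. The premise in Section 3 is that an effect is visible within 3 months in other dermatological diseases, which is not the same as a +2 response, so a high q is unproven. Patients stopped for lack of effect are mostly concordant non-responders, whose loss costs only possible late response. All of this stands. A reader might infer that the contrast is erased, but that holds only at q = 1; the supported statement is dilution if month 6 is used.

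A reader might also infer a bias toward rapamycin, because patients who worsen on rapamycin leave treatment and may be replaced. Assume 10% chance discordance each way and n = 17. The uncorrected test then gives a false rapamycin win in 1.9% of trials. If all placebo-better patients were deleted, this would be P(Bin(17, 0.10) ≥ 4) = 8.3%. The protocol does not say they are deleted. Section 9.2 requires an intention-to-treat analysis, Section 7.6 keeps a visit after withdrawal, and Section 7.5 does not say that earlier data are discarded.

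Finally, it may be said that the visit can wait for the statistical analysis plan. But the visit is part of the primary endpoint, and the switching rule that makes it matter is in the protocol.

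**Conclusion.** The point holds in this form: the primary visit is not fixed, and no rule covers halves switched to open-label rapamycin. If month 6 is used, the comparison is diluted in the discordant pairs that drive the test. On the protocol's own planning assumptions, power drops from 0.90 to 0.35 when half of the switched control halves catch up and to 0.06 when three quarters do. The size depends on q, on how many patients take up whole-face use, and on late response in those who continue blinded; the protocol gives none of these. That the choice of visit remains open after results are seen depends on no such assumption. Neither complete loss of the contrast nor a systematic bias toward rapamycin is established by the text.

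**What to change.** In Sections 7.1.1 and 9.2:

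- **Primary comparison.** Define it as each patient's last standardised photograph under blinded half-face treatment: the 3-month or unscheduled photograph for patients unblinded for efficacy or stopped, and the 6-month photograph for the rest. Naming the 3-month visit is a simpler alternative for patients not unblinded earlier.
- **Photograph before unblinding.** Take one before any efficacy-triggered or patient-requested unblinding. The gap is mainly the patient who insists on stopping. Do not make it a condition for safety code breaks.
- **Analysis set.** Keep all randomised patients in the intention-to-treat analysis and classify each half by the stated definition. A worse rapamycin half beside a placebo half that has not reached +2 is then a concordant non-response, not a placebo-favouring pair.
- **Replacements.** State that patients entered under Section 7.5 are added to stopped patients and do not substitute for them.
- **Post-switch data.** Report them descriptively.

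The cost is protocol wording and one photograph at some unscheduled visits. The downside is that exposure time differs between patients; it is equal for the two halves of each patient, so the paired comparison remains valid. The switching and stopping rules are not changed.

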## 7.2 Randomisation, blinding and treatment allocation

Sides to be treated will be randomized according to a computer randomisation program in blocks of 4. An independent statistician will prepare the randomisation list. Rapamycin and placebo will be packaged in identical bottles with a code number according to the randomisation list. Because of participation of two centres, stratification will take place by allocating entire blocks to a centre. The list of randomisation will be kept at a secure place away from the investigator.

Medication is prepared by Wyeth pharmaceuticals and delivered to the pharmacy of VU Medical Centre Amsterdam. There medication will be labelled with study number and facial side to be treated where LEFT and RIGHT are taken to be determined from the patient’s POV. Patient and physician are blinded until the end of the study.

If at any visit a clear difference arises between treated sides the binding will be broken. If better side is the rapamycin treated one, we will continue with an open-label study. If the better side is the placebo-treated side or the study shows that topical rapamycin has no effect at all, the trial will be terminated prematurely.

Besides unblinding in the situation described above, the code may be broken for a particular subject in case of a suspected serious adverse event. In all other situations unblinding will take place after allocating participants to the relevant analyses populations, just before the primary statistical analysis.

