## 7.3 Study procedures

Conduct of the study

The first visit (screening) includes:
- In- or exclusion, in case of inclusion:

- Physical examination according to protocol, especially lesion size and count
- Biopsy of a representative tumour (if not yet undergone one)

- The patient already has the patient information; this has been sent before the first visit.

- For women: pregnancy test

The second visit (baseline) includes:

- Physical examination according to protocol

- Standardized medical photography of the face. (All photos will be assessed by the investigator and two independent physicians).
- Instruction of patient (see Annex E4), provide study medication according to randomization

Follow-up visits will take place at 3 months and at 6 months. At each follow-up visit, unused study medication will be taken back and new medication is dispensed. Unused medication is weighed to ensure protocol compliance.

At the first follow-up visit at 3 months it will be assessed if unblinding is needed.

Physical examination and medical photography are part of regular care/medical treatment.

Treatment with rapamycin solution (and placebo solution) and pregnancy tests are part of the study.

See also trial flow-chart: Annex F4.

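### The blind can be broken before month 3, but only month-3 and month-6 photographs are analysed, so a patient unblinded early can lack an analysed photograph from the blinded period

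*Protocol*

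**What the plan says.** **When the code can be broken.** Section 3 opens an unscheduled route: "When patients see a difference between the left and right facial side themselves, they can make an earlier appointment". No earliest time is given. The three-month period is an intention ("we aim to continue treatment for at least 3 months"), and it is backed by persuasion: "When patients contact us before the end of this period, we will try to motivate them to continue treatment". The section admits that persuading such patients will be hard, and it ends with a commitment: "However, when a patient really wants to stop treatment due to a clear difference between facial halves, we will break the blinding". Section 7.2 also leaves the time open ("If at any visit a clear difference arises between treated sides"). Section 7.3 names one visit: "At the first follow-up visit at 3 months it will be assessed if unblinding is needed".

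**What follows.** Where the observers have confirmed a difference and the better side proves to be the rapamycin side, section 3 says: "In this case patients are allowed to use rapamycin on the entire face". Section 7.2 likewise moves to an open-label phase.

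**What is measured and analysed.** Section 7.1.1 states: "Per patient 2 photographs will be assessed with the 7-point scale; at 3 months and at 6 months". Each is compared with a baseline photograph. Assessments made by the researcher or the patient at appointments do not enter the analysis. Section 7.3 describes no photograph at an early appointment or before a code break. Sections 3 and 7.3 refer to Annex F4 for further procedures, and that annex is not among the documents.

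**The concern.** Each patient is his or her own control, so the information lies in the period when one half receives rapamycin, the other receives placebo, and nobody knows which. The plan allows that period to end before month 3 but takes its first analysed follow-up reading at month 3. For a patient unblinded in between, no reading from the blinded period is guaranteed to reach the analysis.

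This is not ordinary drop-out. A visible difference between the halves sets it off, so it depends on the outcome. The patients concerned are the likely discordant pairs, and McNemar's test uses no others. Leaving them out, or scoring them from a photograph taken after both halves have had rapamycin, pulls the result toward no difference. Declaring month 3 the analysis visit would not bring them back. A separate analysis plan could not do so either, because it cannot create a photograph that was never taken.

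**Working it through.** **1. The passages side by side**

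| Question | Protocol text | Consequence |
|---|---|---|
| Can the code be broken before month 3? | Section 3 (early appointment; three months an aim; code broken if the patient insists); section 7.2 (any visit) | Yes |
| Must the observers confirm first? | Required on the main route in section 3 (two of three observers, at least 2 points); not stated on the patient-driven route | Not always |
| Is a photograph required first? | Not in sections 3, 7.1.1, 7.2 or 7.3; Annex F4 not shown | Not specified in the main text |
| Would such a photograph be analysed? | Section 7.1.1 assesses month 3 and month 6 only | No, as written |
| Does the contrast survive afterwards? | Section 3 allows whole-face rapamycin on the observer-confirmed route | Diluted by month 3 |

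On dilution, assume a switch at week 8 and a photograph at about week 12. The former placebo half has then had 12 − 8 = 4 weeks of rapamycin, against 12 weeks on the other half.

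**2. The plan's own sample size (section 4.4)**

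Inputs: 35% difference, 90% power, two-sided 0.05, McNemar's chi-square, 17 evaluable patients, 15% drop-out. The protocol gives no discordant rates. I assume 35% respond on the rapamycin side only and none on the placebo side only.

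- Statistic: (b − c)²/(b + c), where b is rapamycin-only and c is placebo-only pairs. With c = 0 it equals b.
- The critical value is 3.84, so the test rejects when b ≥ 4.
- Power = P(B ≥ 4) with B ~ Binomial(17, 0.35) = 0.897, against the stated 0.90.
- Drop-out: 17/(1 − 0.15) = 20, as stated.

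The figures reproduce under this favourable assumption.

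**3. What lost pairs do to the result**

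Expected discordant pairs: 0.35 × 17 = 5.95, about 6, all taken to favour rapamycin.

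| Pairs lost | Pairs left = chi-square | Uncorrected p |
|---|---|---|
| 0 | 6 | 0.014 |
| 1 | 5 | 0.025 |
| 2 | 4 | 0.046 |
| 3 | 3 | 0.083 |

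**4. The same on the power scale**

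Let a share f of responders be unblinded early and counted as non-response. The value of f is an assumption. The observed difference becomes 0.35 × (1 − f), with n = 17.

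| f | Difference | Expected pairs lost, 17 × 0.35 × f | Power |
|---|---|---|---|
| 0% | 35.0% | 0 | 0.90 |
| 10% | 31.5% | 0.6 | 0.83 |
| 20% | 28.0% | 1.2 | 0.74 |
| 30% | 24.5% | 1.8 | 0.63 |

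**The case against.** Several fair points can be made for the protocol.

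- **The observer route implies a reading.** Section 3 asks two of three observers to see at least 2 points, and section 7.1.1 rests assessment on photographs with visual confirmation. A reader might infer that the trigger cannot be documented at an early visit. The text does not support that: a reading before the code break is implied on this route. It is not, however, made part of the analysis, and the patient-driven route does not require it.
- **Annex F4 may schedule a photograph.** Silence in section 7.3 is weak evidence, since that section does not list photography at months 3 and 6 either. This stands. But section 7.1.1 would still not analyse an earlier photograph.
- **Whole-face use is stated for the observer-confirmed route.** A reader might infer that every early-unblinded patient has a worthless month-3 photograph. That does not follow: the patient-driven sentence does not say what is applied afterwards, and even after a switch the contrast is diluted rather than necessarily abolished.
- **Sections 7.2 and 7.3 need not collide.** Section 7.3 does not say that unblinding is considered only at month 3. The wording is loose rather than flatly contradictory.
- **The illustration is a chosen scenario.** With all 20 enrolled patients evaluable, about 0.35 × 20 = 7 pairs are expected, and losing three leaves 4 (p = 0.046). Section 7.5 also replaces patients when numbers fall below 17. This tempers the size. Replacement restores the head count but does not recover the responders whose readings were lost.
- **Few patients may be affected.** The protocol works to hold patients to month 3. Its expectation that one half will improve concerns the study as a whole, not the first three months. This stands.

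**Conclusion.** The gap is real but bounded. As written, a patient whose code is broken before month 3 can have no analysed photograph from the blinded comparison. The loss depends on the outcome and biases toward no difference.

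Its frequency cannot be derived from the document. On the assumed split of 6 to 0 in 17 patients, the uncorrected McNemar test stays significant after two losses (p = 0.046) and fails after three (p = 0.083). If 10% to 30% of responders were lost and counted as non-response, power would fall from 0.90 to between 0.83 and 0.63.

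A reader might infer that a single early unblinding turns a positive trial negative. That needs an exact test (p = 0.031 with 6 pairs, 0.063 with 5). The protocol names McNemar's chi-square and no exact version, so the inference is not supported. Nor does the text show that the fastest responders will in fact go unmeasured, only that they can. Confidence is medium while Annex F4 is unseen.

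**What to change.** In sections 3, 7.1.1 and 7.3:

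1. Require the standardised photographs of both facial halves at any visit where the code may be broken for a side difference, taken before it is opened and whichever route led there.
2. Have the same three observers read them against baseline under the existing rule.
3. State that this reading is the patient's analysed outcome when the code is broken before the scheduled visit.
4. Reconcile the wording in sections 3, 7.2 and 7.3 on when unblinding can occur, and align Annex F4.

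The patient's freedom to stop is untouched. The cost is one extra photo set at a visit that takes place anyway, using existing readers. The drawback is that assessment times will vary between patients. Section 7.1.1 also has each photograph read twice at least two months apart, so the second reading would follow the code break. The protocol should say how allocation is kept from the readers by then.
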